**Fig. 2 Fig2:**
[figure not shown]
Timing and components (ongoing and new) of data collection embedded within a population platform: example of uMkhanyakude, South Africa

In Zimbabwe, the network-based recruitment strategy used to identify and refer YWSS to the DREAMS (intervention sites) or Sisters (in comparison sites) programme, is described in detail elsewhere [8]. This recruitment strategy is appropriate in the absence of a sampling frame and when the population of interest is primarily hidden as is the case among young women who sell sex in Zimbabwe.3)**Process evaluation**: In all four DREAMS evaluation sites, a process evaluation will use both qualitative and quantitative methods to describe DREAMS implementation in context, and to challenge and interrogate causal assumptions in the theory of change [18]. To understand DREAMS’ influence on supply, demand, and uptake of interventions (the ‘prevention cascade’) [12], we will investigate reach and coverage, views and experiences of DREAMS components, what helps and hinders successful implementation and uptake, and to what extent implementation is influenced by differing social and epidemiological contexts.Specifically, we will explore fidelity (whether all components of DREAMS were implemented on schedule and as planned), feasibility (identifying barriers and facilitators to implementation), acceptability (how staff and beneficiaries perceive and value the intervention), and quality (measured by both objective and subjective criteria). In the process, we will aim to identify unexpected pathways and consequences, and who is left out (equity).

The process evaluation will include five methodologies:Qualitative longitudinal study of young people’s experiences. Young people’s experience of and “journeys” through DREAMS, including barriers and facilitators to what works in practice will be tracked in detail for a small cohort of 20 AGYW and, in HDSS sites only, 20 young men in each site. These cohorts – of DREAMS beneficiaries sampled purposively from the general population (for males) and AGYW cohorts (for females) – will be followed longitudinally and offered a range of ways to share their experiences in real-time including use of diaries and informal interviews.Small group discussions. The experiences of AGYW’s families, parents, partners, and broader communities will be explored through focus and family group discussions. Group discussions in each evaluation setting will help investigate understanding and experience of DREAMS and its components and whether social norms and attitudes are influenced by the interventions.Rapid participatory community mapping. This method will be used in the DREAMS areas to quickly gain a broad understanding of the social context for adolescents and young people and the reach and coverage of the AGYW services at baseline and after two years of DREAMS intervention. The mapping will use rapid appraisal methods with participant observation and short interviews.Interviews with key informants in delivery organizations. Up to 20 individuals responsible for implementing DREAMS activities in each setting will be interviewed to explore views and experiences of, and barriers and facilitators to, DREAMS activities each year. Local health care workers and community and youth leaders will also be interviewed.Observations of DREAMS interventions delivered in context. Using checklists, structured observations will record the ways in which DREAMS is delivered and received, and with what quality and intensity (using DREAMS standard operating procedures for reference). Observations will be made of DREAMS interventions in a range of settings such as schools, safe spaces, and health facilities.

### Measurement and analysis of key variables

For component 1, the population-based surveillance in the general population of AGYW and men, the primary comparison is across three time periods: pre-DREAMS, during the early roll-out of DREAMS interventions, and post-DREAMS. The aim is to know whether HIV incidence among AGYW aged 15–24 years (the primary outcome, directly observed through repeat testing) and key secondary outcomes, measured among both AGYW and men, have changed over time at population-level. The primary and secondary outcomes are summarized in Table 2, with secondary outcomes lying on the three pathways of central interest that are between the interventions and HIV incidence: social, behavioural (sexual), and biological protection. The extent to which any changes can be attributed to DREAMS interventions will be assessed in the context of other secular changes, and the findings of the process evaluation. For example, given the background scale-up of universal testing and treatment for HIV, our findings on HIV incidence trends among AGYW will be placed in the context of trends in HIV incidence and the uptake of HIV testing and treatment among those who are not directly targeted for DREAMS HIV prevention interventions.

**Table 2 Tab2:** Primary and secondary measures of impact at the population-level in the South African and Kenyan evaluation sites, to be estimated by comparing calendar time periods that represent pre-DREAMS, during early roll-out of DREAMS, and after DREAMS roll-out

	Adolescent girls and young women		Male sexual partners
	15–19 years	20–24 years	(15–34 years)
Primary Outcome	HIV incidence^a^		HIV incidence^a^
Secondary Outcomes			
*Biological protection*	Knows HIV status^b^		
	HIV/STI prevalence	STI prevalence & Incidence	Uptake of VMMC
			Use of ART
			Community HIV viral load^d^
*Behavioral protection*	Ever had sex		Number of sexual partners (in last year / lifetime)
	Age at first sex		
	Number of sexual partners (in last year / lifetime)		
	Age-disparity with sexual partners		
	Ever been pregnant	Unmet need for contraception^c^	Concurrency of sexual partners
	Age at first / subsequent pregnancies		
	Use of condoms^e^ Any condomless sex		
	Transactional sex		
*Social protection*	In or completed school	In employment or completed vocational / microfinance training	Gender norms: support gender equity
	Age at first marriage		Experience of violence (exposure to / victimization / perpetration)
	Experience of violence		

^a^not collected in Nairobi

^b^know they are HIV+ or have tested HIV negative in the past 12 months

^c^ do not want a child in next 2 years or ever but not using a method to prevent pregnancy

^d^ uMkhanyakude only

^e^ Used condom at last sex (in past 12 months); Any condomless sex in last 1 month / last 12 months and in the last 3 months

For component 2, the nested cohorts of AGYW designed to measure pathways of change, the primary exposure is uptake of DREAMS interventions among individual AGYW, considering single components as well as the number and combination of components of the core package that were received. The extent to which AGYW are aware of, invited into, and participate in DREAMS interventions will be summarized, using the core package and primary/secondary interventions as frameworks to categorise interventions and standardize across the settings. (See Table 3 for proposed, a priori measures of DREAMS uptake.) Comparisons of mediators and secondary outcomes will then be made among AGYW according to their uptake of DREAMS interventions.

**Table 3 Tab3:** Outcomes, mediators of change in the outcomes, and uptake of DREAMS interventions, to be captured via nested DREAMS cohorts of adolescent girls and young women (in Kenya and South Africa) and young women who sell sex (in Zimbabwe)

	AGYW (South Africa and Kenya)		YWSS (Zimbabwe)
	13–17 years^b^	18–22 years^b^	18–24 years
Primary	n/a ^a^		HIV incidence
Secondary Outcomes	Knows HIV status		
	Number of lifetime pregnancies		
	Reduced experience of violence		
	Incidence & prevalence of HSV-2/other STI		HIV prevalence
	Aware of partners’ HIV status		Number of sexual partners
			Engaged in transactional sex for economic reasons
	Age at first sex	Number of sexual partners in the last 12 months	Use of condoms & PrEP with regular/transactional sex partners
	Age at first /subsequent pregnancies	Age at first / subsequent pregnancies	Adherence to HIV treatment and care services
	Condom use		Reduced food insecurity
	Unmet need for contraception		
	Age-disparity with sexual partners	HIV risk of sexual partners (to be defined a priori)	
	No/less transactional sex		
	Stay in school	In employment or completed vocational / microfinance training	
	Age at first marriage or first long-term/live-in partner		
Mediators of change (Sample measures of constructs that DREAMS aims to improve, specifically: social assets, personal safety, self-efficacy, common mental disorders, empowerment, gender equitable norms, and sexual relationship power)	Have at least one trusted female friend they can confide in		Have at least one trusted female friend they can confide in
	Meet regularly in a safe place with peers		Meet regularly at community mobilization sessions with peers and has increased sense of social cohesion
	Know a woman, other than mother/guardian, to turn to if have a serious problem		Can access HIV prevention services including condoms, STI treatment & PrEP (as measure of self-efficacy) and contraceptives
			Is supported to adhere to PrEP, and economically able to adhere/access PrEP
	Able to avoid / refuse sex if sex is not wanted		Has comprehensive knowledge of HIV prevention
	Able to refuse sex if partner will not use a condom (or confident they can use a condom with all sex partners)		Have access to money in an emergency
	Confident they could get a HIV test		Is confident she can negotiate condom use with sexual partners (including clients)
	Confident they can access health services when they need them (sexual and reproductive health services in particular)		Able to avoid violent relationships
	Have access to their own savings		
	Have access to money in an emergency		
	Believes a man and woman should decide together whether to use a condom / what type of contraception to use		
Uptake of DREAMS interventions	• Invited to participate / enrolled in DREAMS • Received at least one DREAMS intervention • Received multiple intervention categories in the DREAMS core package • Received DREAMS primary or secondary interventions (depending on age and need)		Intervention sites (versus comparison sites)
			Within intervention sites, measures of individual uptake will include: • Received at least one DREAMS intervention • Received DREAMS package for key populations (‘KP_Prev’^c^) • Received KP_Prev + educational subsidies or vocational training • Received KP_Prev + PrEP

^a^In South Africa and Gem, Kenya, HIV incidence will be estimated from the larger population-level studies (see Table 2), for adequate statistical power (see ‘Sample Sizes’ below)

^b^ Age at enrolment, to be followed over two years

^c^‘KP_Prev’ is the PEPFAR indicator used to measure DREAMS package for key populations and includes condom promotion, HIV testing services, and social asset building [22]

‘Mediators of change’ (Fig. 1 and Table 3) will be measured at the individual level, representing the DREAMS Partnership’s commitment that the interventions will increase determination, resilience, empowerment, social assets, and personal safety among AGYW.

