#### Gem sub-county, Siaya county, Kenya

The Kenya Medical Research Institute (KEMRI)/Centers for Disease Control and Prevention (CDC) HDSS site in Siaya County of western Kenya covers a total population of approximately 223,000 people and 55,000 households, with demographic surveys three times a year. Siaya County includes three sub-counties: Rarieda, Siaya, and Gem. For the evaluation of DREAMS, the KEMRI/CDC platform in Gem will be used, as this is where HIV surveillance has been conducted most frequently and recently, i.e., three behavioral surveys and four rounds offering HIV testing services in 2011/2012, 2013/14, 2016, and 2017, among a random sample of one-quarter of all households and all resident members of those households as an open cohort [13].

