#### Sample sizes

HIV incidence - the primary endpoint for the impact evaluation - will be measured using HDSS data in uMkhanyakude and Gem, and data from the cohorts of young women who sell sex in Zimbabwe. In uMkhanyakude, HIV incidence was ~ 6 per 100 person-years among AGYW aged 15–24 years old during 2011–2015, and ~ 4.6 and ~ 7.5 per 100 person-years among those aged 15–19 and 20–24 years respectively, based on a total of 7687 person-years of follow-up. Assuming, conservatively, that there will be ~ 3000 person-years of follow-up during 2017–2019 (40% of 7687), [20] then study power is > 90% to show an overall reduction in HIV incidence of 30, and > 90% in sub-group analysis of AGYW aged 15–19 and 20–24 years to show a 40% reduction in HIV incidence (Fig. 3a). In Gem, western Kenya, HIV incidence was ~ 0.7 per 100 person-years among AGYW aged 15–24 years during 2011–2016, based on a total of 8236 person-years of follow-up [21]. (Whereas sero-surveys are conducted annually in uMkhanyakude, they are less frequent in Gem: data are available from three sero-surveys in Gem between 2011 and 2016. Sero-conversions observed during this period, including those estimated from the 2016 survey, will be considered ‘pre-DREAMS’ because they are unlikely to be influenced by DREAMS by this early stage of implementation.) During 2017–2019, all AGYW in Gem will be sought for participation in the HDSS; with a participation rate of 70% in each year, and an annual out-migration rate of 20%, it is estimated that there will be ~ 9000 person-years of follow-up during 2016–2019. Study power is low to show a change in HIV incidence in sub-group analyses of AGYW aged 15–19 and 20–24 years, but ~ 80% to show an overall reduction of 45, and 90% to show an overall reduction of 50% in HIV incidence (Fig. 3b).

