**Fig. 3 Fig3:**
[figure not shown]
Study power for comparing HIV incidence between post-DREAMS and pre-DREAMS time periods in (**a**) uMkhanyakude, South Africa and (**b**) Gem, Kenya

The same sample sizes will also allow us to detect meaningful change in secondary outcomes that are more common among AGYW than HIV incidence, including knowledge of HIV status and use of condoms (Additional file 1: Table S2). Secondary outcomes will also be measured at the population level for men including the proportion of males who know their HIV status, uptake of voluntary male medical circumcision among HIV-negative males, and uptake of anti-retroviral therapy among HIV-positive males (Additional file 1: Table S3).

For the nested cohorts in the three HDSS sites, selected from the HDSS sampling frames in South Africa and Western Kenya, a minimum of 400 girls in each of the 13–17 and 18–22 year age groups will allow us to analyze causal relationships between key mediators and key outcomes (Additional file 1: Table S4), and similarly to analyze causal relationships between uptake of DREAMS interventions and key outcomes. Over-sampling by 20% will cater for non-response and loss-to-follow-up. In Nairobi, for the additional cohort of 400 younger girls aged 10–14), the sample size of 400 will allow us to explore pathways between uptake of DREAMS interventions, key mediators and age-appropriate outcomes like school completion.

In Zimbabwe, network-based recruitment will be used to enroll 18 to 24-year-old women who sell sex from intervention and comparison sites. Based on the assumption that 20% of YWSS identified through this process will test HIV-positive and 30% of HIV-negative YWSS will be lost to follow-up over 24 months, it is estimated that 1200 women from the intervention and comparison sites (2400 total) will be needed to detect a 40% reduction in HIV incidence [8]. This sample size is also sufficient to explore pathways linking DREAMS to secondary outcomes.

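### In Gem, the outcome 'Knows HIV status' does not separate the study's own HIV tests from other tests, and study testing becomes more frequent after DREAMS, so the pre/post contrast can rise with no DREAMS effect

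*Protocol article*

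**What the plan says.** Table 2 lists knowledge of HIV status as a secondary outcome under biological protection. Footnote b defines it as those who "know they are HIV+ or have tested HIV negative in the past 12 months". No source of test is named. The Table 2 outcomes are "to be estimated by comparing calendar time periods that represent pre-DREAMS, during early roll-out of DREAMS, and after DREAMS roll-out". The Analysis plan applies to secondary outcomes the same periods as for HIV incidence, so in Gem everything up to and including 2016 is pre-DREAMS and 2017–2019 is post-DREAMS.

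The Gem paragraph under Study settings reports "four rounds offering HIV testing services in 2011/2012, 2013/14, 2016, and 2017, among a random sample of one-quarter of all households". The Sample sizes section adds: "Whereas sero-surveys are conducted annually in uMkhanyakude, they are less frequent in Gem". It then gives the post-DREAMS plan: "During 2017–2019, all AGYW in Gem will be sought for participation in the HDSS; with a participation rate of 70% in each year". The same sentence assumes 20% out-migration a year. The paragraph after Fig. 3 says that the same sample sizes allow meaningful change to be detected in commoner outcomes, "including knowledge of HIV status and use of condoms".

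**The concern.** HIV testing services are part of the DREAMS core package (Table 1). They are also what the Gem surveillance rounds offer. Under footnote b, a negative result from a survey and one from a DREAMS provider count the same.

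That would matter little if study testing ran at a constant rate, but in Gem it changes at about the boundary between the periods compared. Before DREAMS, a woman's previous study test was usually about two years old at interview, outside the 12-month window. From 2017 it may be about one year old, and so may fall inside.

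The shorter interval is the cause. Counted study tests can only push the post-DREAMS value up, in the direction of a programme benefit, on an outcome that the article names among those it can detect change in.

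**Working it through.** **The plan's own figure.** The only Gem calculation shown is power for HIV incidence: about 80% for a 45% reduction and 90% for a 50% reduction.
- Inputs: 0.7 per 100 person-years, 8236 person-years before and about 9000 after. Two-sided alpha of 0.05 is my assumption.
- Expected events: 0.007 × 8236 = 57.65 before; 0.007 × 0.55 × 9000 = 34.65 after a 45% reduction; 0.007 × 0.50 × 9000 = 31.5 after a 50% reduction.
- Log rate ratio, 45%: |ln 0.55| / √(1/57.65 + 1/34.65) − 1.96 = 0.598/0.215 − 1.96 = 0.82, power 79.4%. For 50%: 87.9%.
- Difference in rates with pooled variance: 80.3% and 88.8%.

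The stated power is reproduced to within about 2 points, so the follow-up assumptions agree with the text. The present point does not alter that figure. The calculations for knowledge of status are in a supplementary table that is not shown.

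**Intervals between study tests in Gem.**
- 2011/12 to 2013/14: about two years.
- 2013/14 to 2016: two to three years.
- 2016 to 2017, and between rounds in 2017–2019: about one year, inferred from participation being stated for each year.

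**Model.** Let b be the share who know their status from non-study sources, and c the share of those interviewed who hold a study test inside the 12-month window. If the two are independent:

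observed share = 1 − (1 − b)(1 − c); spurious rise = (1 − b) × (c after − c before).

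**Inputs for c.**
- Before DREAMS, c is taken as 0 because of the intervals above. Any in-window tests before DREAMS would shrink the rise.
- In a later post-DREAMS round, the share with a study test at the previous round is 0.70 × 0.80 = 0.56 (participation × not replaced through migration).
- In the first round that seeks all AGYW, only the quarter from previously sampled households can hold an earlier study test: 0.56 / 4 = 0.14. This assumes that the 2016 round also had 70% participation.
- Mean over three equally weighted rounds: (0.14 + 0.56 + 0.56) / 3 = 0.42.

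**Results with b = 0.50 and no DREAMS effect.**
- All previous tests in the window: 0.50 × 0.42 = 0.21, so 50% becomes 71%. By round the rise is 7, 28 and 28 points.
- Half in the window: 0.50 × 0.21 = 0.105, so 50% becomes 60.5%.
- None in the window: no rise.

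**Other values of b, with mean c of 0.21 to 0.42.**
- b = 0.30: 0.70 × 0.21 to 0.70 × 0.42 = 14.7 to 29.4 points.
- b = 0.70: 0.30 × 0.21 to 0.30 × 0.42 = 6.3 to 12.6 points.
- Zero remains possible at every b.

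**The 2017 round.** The Gem paragraph lists 2017 as a quarter-household round, whereas Sample sizes seeks all AGYW from 2017. If the expansion came only in 2018, the three values of c would be 0.56, 0.14 and 0.56, with the same unweighted mean of 0.42. The mechanism does not depend on which text is right.

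**The case against.** **Footnote b is a one-line indicator in a condensed article.** Whether survey tests count, when in the interview status is asked, and how the window is applied may be settled in questionnaires, the site protocols or the SAP. This stands in part. A reader might infer that the outcome must rise, and the article does not support that. If status is scored after the current round's own test, both periods are affected alike. If it is asked before, rounds about 12 months apart sit on the edge of the window. The definition as written nevertheless admits study tests, and nothing shown separates them.

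**Wider household coverage.** A reader might blame the move from a quarter of households to all. That does not hold. Pre-DREAMS values come from the sampled households themselves, and newly covered AGYW have no earlier study test at their first round, so the expansion dilutes the effect at first. Nor is every AGYW tested every year: all are sought and 70% are expected.

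**Size.** A reader might put 0.70 in for every post-DREAMS round and obtain 0.50 × 0.70 = 35 points. That ignores both the out-migration stated in the same sentence and the first expanded round. All versions also assume that participation means a test with a known result, and that study and routine testing are independent.

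**Nested cohorts.** A reader might extend the point to them, since Table 3 also lists knowledge of status. No text says that the Kenyan or South African cohorts test for HIV. Their main contrast is by individual uptake, which uniform testing would not by itself favour.

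**Safeguards.** The small-area dose-response analysis helps, because testing offered uniformly creates no gradient. It does not repair the pre/post contrast, which is the primary way of measuring impact. Reading changes against secular trends need not help either: the worked example concerns HIV incidence and background testing and treatment, and the intensified study effort is described for AGYW only.

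**Conclusion.** The point holds as a possible bias towards DREAMS in one secondary outcome in one setting. In Gem, footnote b counts study tests along with all others, and the interval between study tests shortens from about two years to about one as the post-DREAMS period begins. A pre/post rise cannot then be separated from the evaluation's own testing.

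For 50% routine knowledge the spurious rise averages about 10 to 21 points, depending on whether half or all of the previous tests fall in the window. It is zero if none do or if status is scored after the round's own test. These sizes are illustrations. They rest on an assumed baseline, three equally weighted rounds, 70% participation that includes testing, 20% out-migration, and independence of study and routine testing.

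The point is specific to Gem. Sero-surveys in uMkhanyakude are described as annual, and Nairobi has had no serological survey since 2007. The incidence analysis and its power are unaffected.

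**What to change.** - In Gem, keep the footnote-b definition and also report the outcome by source of test, surveillance versus outside. Use the reported place of last test, or match reported tests to the study's own test dates. Apply one rule in all periods, and state it in footnote b.
- Do not attribute a pre/post rise to DREAMS unless it also appears in the version that excludes surveillance tests.
- State whether status is asked before or after the current round's own test.
- Carry the rule to a nested cohort in Table 3 only if that cohort tests for HIV.
- Reconcile the Gem paragraph, which lists 2017 as a quarter-household round, with Sample sizes, where all AGYW are sought from 2017.

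The cost is one added definition and a lookup, provided that test source or matching dates were recorded in every period. The downside is that survey testing may displace routine testing, so the outside-only version can understate a DREAMS effect. That is why both versions should be reported.

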DREAMS investments aim to ensure that AGYW in selected DREAMS areas (sub-national units with high HIV burden) have access to all core package interventions, either through DREAMS funding or additional PEFPAR funding schemes (e.g., for VMMC) or coordination with national government programmes (e.g., for cash transfers or educational subsidies). PrEP is planned for selected countries and sites within countries, as determined by national governments. Guidance for each component of the core package has been provided to countries by PEPFAR, and coverage targets have been set for each sub-national unit by age group, area and intervention [9]. ‘Primary’ interventions are the priority interventions from the core package that all AGYW in an age group should receive. ‘Secondary’ interventions are needs-based interventions from the core package, recommended for specific sub-populations of AGYW based on additional circumstances, e.g., condom provision for AGYW who are sexually active; post-violence care for those who have experienced sexual violence. Additional file 1: Table S1 summarises the primary and secondary interventions in each country setting.

The way in which the various DREAMS components are rolled out and coordinated, and the timing of implementation will differ in each evaluation site, depending upon: the capacity and readiness of Implementing Partners (IPs) contracted by the United States Government to implement DREAMS services; the timing of contractual arrangements with IPs; negotiations with national governments; finalization of sex education curricula for schools; and other contextual factors. Given the heterogeneity in DREAMS’ delivery, we will monitor how, when, by whom, and to whom, components of the DREAMS package are delivered, in the process evaluation activities described below [10].

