To achieve the above, the design comprises three main components:**Population-based surveillance systems**: In uMkhanyakude, and Gem and Nairobi in Kenya, existing surveillance systems that link HIV, demographic, behavioural, and service uptake data, will be used and enhanced in order to assess the population-level effects of DREAMS over time (in relation to the timing of DREAMS roll-out) among AGYW, men who are in the age range that includes most of the partners of AGYW, and also older adults who may receive DREAMS interventions that are directed at the wider community. In uMkhanyakude and Gem, linkage to HIV clinic data is possible and geospatial data are available, and in uMkhanyakude HIV phylogenetics data are also available. We will utilise historical (for baseline) and prospective data (for comparison) from the population-based systems (see Fig. 2 for example in South Africa).**Cohorts of AGYW**, randomly selected from the total population: For detailed study of the pathways by which DREAMS interventions influence HIV risk, we will establish cohorts of AGYW within each evaluation site. Cohort enrolment will be completed during the early roll-out of DREAMS interventions, during 2017, and those enrolled will be followed prospectively, at ~ 12 and ~ 24 months later. There will be more detailed and comprehensive data collection on uptake of DREAMS interventions, mediators of change, and socio-economic, behavioural and health outcomes than is possible in the total population. In the Zimbabwe setting, the same cohort used to measure the overall impact of DREAMS interventions on HIV incidence among YWSS can be used to analyse pathways of change.In uMkhanyakude, Nairobi, and Gem, nested cohorts of AGYW aged 13–22 will be selected using the HDSS census population as the sampling frame. A random sample of AGYW stratified by age (13–17 and 18–22 years) and area of residence will be selected. The Nairobi evaluation will further recruit a sample of young girls from age 10 (building on the Global Early Adolescent Study pilot in this setting), resulting in three age groups for the cohorts: 10–14, 15–17, and 18–22 years.

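### The printed definition of unmet need for contraception (Table 2, footnote c) has no sexual-activity condition, so the indicator can rise when sexual activity falls

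*Protocol article*

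**What the plan says.** In the protocol article, section 'Measurement and analysis of key variables', Table 2 lists the secondary outcome "Unmet need for contraception^c" under behavioural protection, in the 20–24 years column as the table was extracted. Footnote c defines it by two conditions only: "do not want a child in next 2 years or ever but not using a method to prevent pregnancy". Neither the footnote nor any other part of the article adds a condition on sexual activity or restricts the base.

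The setting for Table 2 is "the population-based surveillance in the general population of AGYW and men". The same block of the table lists ever having had sex and "Age at first sex" as outcomes for AGYW, so women who have not had sex belong to the population.

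Table 3, for the nested cohorts, lists "Unmet need for contraception" again, with no definition. Its own footnote c concerns a PEPFAR indicator for key populations. These cohorts start younger: "nested cohorts of AGYW aged 13–22 will be selected using the HDSS census population as the sampling frame".

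Elsewhere the article does tie measures or need to sexual activity. Footnote e of Table 2 bases condom use on the last sex within 12 months. 'The DREAMS core package' gives, as an example of a needs-based intervention, "condom provision for AGYW who are sexually active".

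**The concern.** Unmet need is meant to capture women at risk of a pregnancy they do not want who lack protection. A woman who is not having sex is not at that risk, yet the printed rule scores her as unmet need if she wants no child soon and uses no method.

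This matters more here than in a descriptive survey, because sexual activity is itself something the evaluation expects to change. Later sexual debut is an outcome in the same table, and one of the mediators in Table 3 that DREAMS aims to improve is "Able to avoid / refuse sex if sex is not wanted". If the programme works through that route, women move out of sexual activity. Under footnote c, any of them who would otherwise have used a method become new cases of unmet need. The indicator then moves in the unfavourable direction for a reason unrelated to access to contraception, and a true gain in contraceptive use among active women is diluted or hidden. 'Analysis plan' compares the secondary outcomes across the pre-DREAMS, early roll-out and post-DREAMS periods, so a shift in sexual activity between periods feeds directly into the comparison.

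**Working it through.** The article gives no rate, sample size or power for unmet need in its main text, so there is no figure to reproduce. The check is of direction, followed by illustrations in which **every rate is assumed**.

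**Notation**
- w: share of women who want no child in the next 2 years or ever
- a: share who are sexually active
- c: method use among active women who want no child
- c0: method use among women who are not active

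**Indicator as printed:** U = w[(1 − a)(1 − c0) + a(1 − c)].
Its slope in a is w(c0 − c). Whenever active women use methods more than abstinent women (c > c0), U rises as a falls. With c0 = 0, U = w(1 − a·c).

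**With a sexual-activity condition:** w·a·(1 − c) as a share of all women, or 1 − c among active women who want no child.

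**Illustration at 20–24 years** (w = 0.95, c = 0.50, c0 = 0; activity falls from 70% to 60%)

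| | a = 0.70 | a = 0.60 |
|---|---|---|
| As printed, w(1 − a·c) | 0.95 × 0.65 = 61.75% | 0.95 × 0.70 = 66.5% |
| Active with unmet need, share of all | 0.95 × 0.70 × 0.50 = 33.25% | 0.95 × 0.60 × 0.50 = 28.5% |
| Among active women wanting no child | 50% | 50% |
| Abstinent share of those scored as unmet need | 0.30/0.65 = 46% | 0.40/0.70 = 57% |

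The printed indicator rises by 4.75 points, while the burden among active women falls by 4.75 points of all women.

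**Masking.** At a = 0.60 the printed indicator improves on its starting value only if a·c exceeds 0.70 × 0.50 = 0.35. Method use among active women would have to exceed 0.35/0.60 = 58.3% before any improvement showed. A second case: w = 0.90, c0 = 0, activity from 50% to 40%, method use from 50% to 60%. The printed indicator goes from 0.90 × (1 − 0.25) = 67.5% to 0.90 × (1 − 0.24) = 68.4%, although unmet need among active women wanting no child falls from 50% to 40%.

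**Boundary case.** With w = 0.90 and a = 0.50, c = 0.50, method users are 25% of women. If only non-users delay sex, that 25% does not change and the indicator stays at 0.90 × 0.75 = 67.5%.

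**Range.** Taking w = 0.8 or 0.9, c = 0.2, 0.5 or 0.7, c0 = 0 or 0.1, and activity falling from 30% to 20%, 50% to 40% or 80% to 75%, the printed indicator rose in every combination, by 0.4 to 6.3 points. Abstinent women made up 22% to 89% of those scored as unmet need before the fall. With the condition added, the indicator fell (all-women base) or did not change (active-women base).

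**The case against.** The best defence is that footnote c is a one-line gloss in a condensed article. It does not say that the base is all AGYW, other entries that presuppose a partner also state no base, and site protocols, which the article says are available on request, may restrict the denominator. The remark on condom provision describes the programme and not the derivation of this outcome. Part of this stands: the restriction may exist elsewhere. But the article chose to print an operational definition, gave recall windows in the neighbouring footnotes, and measures Table 2 in the general population. The printed rule is incomplete as it stands.

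Several stronger readings are tempting and the article does not support them:

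- **That every abstinent girl is scored as unmet need.** Only those who want no child and use no method are, and a questionnaire that codes abstinence as a method would remove them.
- **That the indicator must worsen when sex is delayed.** The boundary case shows no change if only would-be non-users delay.
- **That the measure mostly counts abstinent women.** In the illustration for 20–24 years they are 46% at the start, and the share depends wholly on assumed rates.
- **That girls of 13–17 years are affected by this definition.** Footnote c is attached in Table 2 only, and Table 3 gives no definition. An effect at 13–17 years arises only if footnote c is carried over.
- **That a protective effect would be reported as harm.** Sexual debut, partner numbers and condom use appear in the same table, so a change in activity would be visible beside this indicator.
- **That currently pregnant women should simply be excluded.** Some are pregnant because earlier need was unmet, so that is a contestable choice on which the article is silent.

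**Conclusion.** The concern holds for the Table 2 outcome at 20–24 years. As printed, footnote c counts women who are not sexually active, want no child and use no method as having unmet need. The direction of the distortion follows from the definition alone, provided that active women use methods more than abstinent women: less sexual activity raises the indicator, or leaves it flat when only would-be non-users delay.

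The size cannot be taken from the article. The move from 62% to 67% against a fall from 33% to 29%, and the range of 0.4 to 6.3 points, rest entirely on assumed rates. The article gives no basis for a ten-point fall in activity at these ages.

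For Table 3 the finding is that no definition is given. If footnote c were carried over, the effect would be larger at 13–17 years, where fewer girls can be expected to be sexually active; that too is an assumption. The point is worth correcting because an incomplete rule is in print and the correction is cheap. It touches one secondary outcome among many and leaves HIV incidence and the power statements as they are.

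**What to change.** Amend footnote c as follows:

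1. Add a sexual-activity condition with a stated recall window, for example sex in the past 12 months, which matches the window already used in footnote e.
2. Report the outcome on two named bases: among sexually active AGYW, and as a share of all AGYW. The first isolates contraceptive use; the second shows the population burden.
3. State how currently pregnant women are classified, without excluding them by default.
4. State whether abstinence may be recorded as a method.
5. Cross-reference the same definition from the Table 3 outcome.

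The cost is a change to a derived variable and a few lines of text. Table 2 already calls for ever having had sex, partners in the last year and condom use with a 12-month window, so the sexual-activity condition should need no new question. Current pregnancy status is not listed as such in the tables (they give pregnancy history), so its availability should be checked at each site before the classification is fixed.
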